## Abstract

**Background:**

During the first period of life, critically ill as well as healthy newborn infants experience recurrent painful procedures. Parents are a valuable but often overlooked resource in procedural pain management in newborns. Interventions to improve parents’ knowledge and involvement in infants’ pain management are essential to implement in the care of the newborn infant. Neonatal pain research has studied a range of non-pharmacological pain alleviating strategies during painful procedures, yet, regarding *combined* multisensorial parent-driven non-pharmacological pain management, research is still lacking.

**Methods/design:**

A multi-center randomized controlled trial (RCT) with three parallel groups with the allocation ratio 1:1:1 is planned. The RCT “Parents as pain management in Swedish neonatal care – SWEpap”, will investigate the efficacy of combined pain management with skin-to-skin contact, breastfeeding and live parental lullaby singing compared with standard pain care initiated by health care professionals, during routine metabolic screening of newborn infants (PKU-test).

**Discussion:**

Parental involvement in neonatal pain management enables a range of comforting parental interventions such as skin-to-skin contact, breastfeeding, rocking and soothing vocalizations. To date, few studies have been published examining the efficacy of combined multisensorial parent-driven interventions. So far, research shows that the use of combined parent-driven pain management such as skin-to-skin contact and breastfeeding, is more effective in reducing behavioral responses to pain in infants, than using the pain-relieving interventions alone. Combined parental soothing behaviors that provide rhythmic (holding/rocking/vocalizing) or orogustatory/orotactile (feeding/pacifying) stimulation that keep the parent close to the infant, are more effective in a painful context. In the SWEpap study we also include parental live lullaby singing, which is an unexplored but promising biopsychosocial, multimodal and multisensory pain alleviating adjuvant, especially in combination with skin-to-skin contact and breastfeeding.

**Trial registration:**

ClinicalTrials.gov (NCT04341194) 10 April 2020.

## Background

Parents are a valuable but often overlooked resource in procedural pain management in newborn infants. The influence of the parent is particularly salient in early infancy and in extremely distressful situations such as painful procedures, because infants lack the resources to successfully self-regulate. Therefore, infants need an emotionally available and stable parent who responds adequately to the infant’s distress signals and who is able to soothe, regulate and share the infant’s states [1]. In the Nordic countries today, the concept of family-centered care (FCC) is considered best practice in the care of the newborn [2, 3]. Since the 1990s, FCC has been and still is, part of an ongoing paradigm shift where family involvement in the infant’s care and the parent-infant relationship are of central importance, a cornerstone in current neonatal and pediatric health care [4, 5]. Nonseparation of parents and infants is a protective measure in decreasing stress in both parents and infants [6] and should also be applied in painful procedures [7].

As part of routine postnatal care, all infants experience recurrent painful procedures early in life with blood sampling for newborn metabolic screening and immunization programs. Infants in the neonatal intensive care unit (NICU) receive the highest amount of pain exposure, on average between 7 and 17 painful procedures per day [8]. Far from all infants receive adequate pain management during procedures (Shah & Siu 2019, [9, 10]). Untreated pain leads to unnecessary suffering but also leaves the newborn infant at risk for long term negative consequences from the pain. Research have shown detrimental effects of repeated painful experiences in the newborn infant including altered cortical development [11, 12], altered pain processing, increased internalizing behavior [13] and long-term effects on cortisol response [14]. For infants born preterm, neonatal pain-related stress was associated with alterations in both early and in later developmental outcomes [15].

During the last decade, parents’ participation in infant pain management has become a focus for research in nursing pain science (e.g. [16–20]). Parental presence has been shown to increase documentation of nursing pain assessment and of the use of non-pharmacological pain-relieving methods such as skin-to-skin contact (SSC) and breastfeeding, and decrease the infant’s pain intensity and behavioral distress [21, 22]. Parents have a unique knowledge and perspective of their infant’s needs and personality and can be effective partners in the care of the infant, including pain management, if they are acknowledged by the health professionals [20, 23]. Not all parents are able to provide emotional and physical closeness, many parents do not know how to effectively comfort their child during a medical procedure, and some do not feel confident doing so [24]. But most parents experience a feeling of helplessness in their inability to protect their infant from pain during procedures [25, 26]. Therefore, health professionals need to safeguard parent-infant proximity, reciprocity, and establishment of parental responsibility, which are all essential factors for the parent-infant attachment process [26]. Interventions to improve parents’ knowledge and involvement in infants’ pain management are essential to implement in the care of the newborn infant [26]. Parents need to and want to participate actively in their infant’s pain management, and parents should receive education and guidance in various format, not just verbal information, on how to mitigate their infant’s pain [23, 24, 27–31].

Pain alleviating pharmacological agents such as oral sweet solutions, i.e. sucrose and glucose, are today part of standard care in neonatal and postnatal care and are considered to have a calming and analgesic effect on infants during painful procedures [32]. Sweet solutions have been extensively investigated and found to reduce procedural pain from blood-sampling procedures in preterm, term infants and infants ≤12 months old, without serious side effects [33]. However, there is a consensus that non-pharmacological strategies should be the first choice in procedural pain management for infants because there are no adverse effects and parents can be involved using these approaches safely [23, 34, 35]. Non-pharmacological pain management involves interventions driven by nurses and/or parents. Just like oral sweet solutions, swaddling, containment or facilitated tucking, positioning, non-nutritive sucking and recorded music stimulation, are nurse-initiated pain alleviating interventions where parents can be included but parental presence is not required [32, 36]. Among the non-pharmacological approaches, the biopsychosocial perspective strongly supports parent-driven interventions [37]. In the parent-driven non-pharmacological interventions, the parent herself/himself is a mediator for pain relief [36]. Parent-driven non-pharmacological interventions are consistent with modern family-centered care in which the best interests of the infant and family are put ahead of staff convenience [36]. SSC, breastfeeding and live singing are simple and cost-effective evidence-based interventions that may modify the infant’s pain and stress if the strategies are well-timed [38–41]. SSC is a method widely used in postnatal care globally. A significant amount of research has also shown the pain-relieving effect of skin-to-skin contact during painful procedures in newborn infants [19, 42]. Breastfeeding has demonstrated efficacy that is equal to, or greater than, sweet taste interventions in reducing behavioral and physiological responses to pain in full-term infants undergoing venipuncture with no demonstrated adverse outcomes [38]. Live parental infant-directed lullaby singing, informed by music therapy research, has not been previously investigated during painful procedures. It has been confirmed in previous research in non-painful contexts that live parental lullaby singing is an individually tailored, non-verbal, multisensory, affective, relationship-based tool useful in regulating the infant, augmenting the parent’s focus on the infant in the moment, enhancing the parent’s emotional availability and responsiveness and decreasing stress in the dyad [43–45]. Previous research with recorded music stimulation with instrumental lullaby music, selected in consultation with an accredited music therapist, has shown similar effect to the current gold standard of oral sucrose [46], and the combination of music stimulation with sucrose provides better pain relief during blood sampling than when sucrose or music is used alone [46]. Recorded mother’s voice has also shown similar pain alleviating effects as oral sweet solutions [47, 48].

Neonatal pain research has studied a range of non-pharmacological pain alleviating strategies during painful procedures. However, there is a dearth of research about combined multisensorial parent-driven non-pharmacological pain management, which encompasses a combination of individual pain-relieving interventions such as parental closeness and SSC, olfactory, oral and auditory stimulation. Therefore, a multi-center randomized controlled trial with the aim to investigate the efficacy of combined pain management with SSC, breastfeeding and live parental lullaby singing, is planned in postnatal care.

## Methods: hypothesis, participants, interventions, measures and outcomes

### Hypothesis

No previous research has assessed the efficacy of combined parent-driven pain management with SSC, breastfeeding and live parental lullaby singing in newborn infants during routine newborn metabolic screening. In this research study, “**P**arents **a**s **p**ain management in **Swe**dish neonatal care – **SWEpap**”, we hypothesize that parent-driven pain management such as SSC in combination with breastfeeding and live parental lullaby singing, will provide a more effective pain management during venipuncture in newborn infants compared to standard pain care initiated by health care professionals.

### Study design

This is a multi-center, randomized controlled trial (RCT) with three parallel groups with the allocation ratio 1:1:1.

### Study setting

This RCT involves parent-infant dyads recruited from four health care regions in Sweden during the routine newborn metabolic screening. In the Swedish context, the healthy newborn infant is often discharged soon after birth and returns at 48 h of age for a newborn screening test and medical examination. The involved regions represent both university hospitals and regional hospitals.

### Eligibility criteria

Healthy newborn infants, who will be screened with the routine newborn metabolic screening test and their parent are enrolled. Infants treated with sedatives or analgesics within the last 24 h are excluded. A written informed consent is acquired from the infant’s parents. Parents who understand Swedish or English are eligible for inclusion. The infant-parent dyad is randomly assigned to one of three treatment groups; one standard of care group with glucose (*n* = 75), one group with skin-to-skin contact (n = 75), and one group where skin-to-skin contact is combined with breastfeeding (if applicable) and live parental lullaby singing (n = 75), (Table 1).

**Table 1 Tab1:** Treatment groups

Group	Treatment	Treatment description
Group 1	Standard care with glucose	The infant is placed on the examination table for the blood test. Standard care comprises facilitated tucking done by a nurse or the parent, 1–2 ml of oral glucose (300 mg/ml) given in fractioned doses from 2 min before the procedure and the opportunity to suck on a pacifier or on a parent’s or a nurse’s plastic gloved finger.
Group 2a	Parent-driven pain management with skin-to-skin contact	The parent will sit in an adjustable recliner chair during the procedure and the infant will be placed naked (except for a diaper and possibly a hat) on the parent’s bare chest 10 min before the venipuncture. The skin-to-skin contact will proceed during and a while after the procedure.
Group 2b	Parent-driven pain management with skin-to-skin contact and breastfeeding	The parent will sit in an adjustable recliner chair during the procedure and the infant will be placed naked (except for a diaper and possibly a hat) on the parent’s bare chest 10 min before the venipuncture. Breastfeeding starts about 2 min before the venipuncture and the blood test is performed when the infant is latched and sucking well.
Group 3	Parent-driven pain management with a combination of skin-to-skin contact, breastfeeding and live parental lullaby singing	The intervention in the combination group will follow the above described skin-to-skin and breastfeeding treatment descriptions. The parents are also instructed to hum a lullaby with their infant. The parent starts humming the lullaby when the infant is placed on the parent’s bare chest 10 min before the venipuncture and continues during and a while after the procedure. The humming should be performed in a simple, repetitive, soft and sedative mode in a low pitch, in consonant harmony, with a slow, steady and predictable pulse of 3/4 or 6/8 rhythm, maintaining a constant sound level between recommended ≤55–65 dB on the A-scale [49].

### Interventions

The treatment groups in the RCT are described in Table 1. Group 2, comprising SSC, is divided into two subgroups, one with only SSC and one where the mother also chooses to breastfeed her infant during the test. The reason for these subgroups is that standard of care in one of the hospitals does not include glucose but comprises only SSC and breastfeeding when applicable. To ensure intervention fidelity in the live parental lullaby singing, a short video, showing a parent who sings according to the treatment description of the lullaby singing, will be played for the parents who are randomly assigned to group 3. These parents will also be verbally guided in how to sing before the intervention starts. The verbal instructions are simplified and delivered in dialogue with the parent who can ask questions.

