### Sample size

No previous RCT has examined the effects of parent-driven pain management in newborn infants by combining SSC, breastfeeding and live parental lullaby singing. Based on previous studies using PIPP-R or its predecessor PIPP in pain alleviation projects, a difference of two PIPP-R points between standard care (group 1) and the full parent driven pain management (group 3) is considered clinically important. Based on those studies we also assume a standard deviation around 2 points. A power calculation sets the number of infants to include in the study to 63 in each group, with a power of 0.8 and a significance level set to 0.05 (www.clincalc.com). To compensate for possible dropouts, incomplete data, such as equipment malfunction or blood sample collection failure, 75 infants per group will be enrolled, making a total of 225 infants.

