### Recruitment and allocation

The researcher in each region will present the study and provide written information about the study to eligible parents before they are discharged from the hospital (Fig. 1. Timeline SWEpap study). When the parent-infant dyads return to the postnatal care unit for the metabolic screening test, they will be asked to participate and to sign the consent form (both the mother and her partner). The parents who have accepted to participate are then randomly assigned to one of the three interventions groups using the sealed opaque envelope system with randomly generated treatment allocations administered by an impartial researcher. Once the parents have consented to enter the trial, the researcher opens the envelope and the allocated treatment regimen is offered to the parents. The researchers will then guide the parents in each group how to position themselves and the infant and if applicable how to use live parental lullaby singing. If the parent does not adhere to the protocol in the allocated treatment group, the infant will be excluded from the study.

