### Data analyses, management and monitoring

Methods for statistical analyses are chosen depending on scales of measurement and normal distribution. The data will be analyzed with descriptive and comparative statistics. Continuous variables that are normally distribute will be presented with mean and standard deviation and compared with t-test for two groups and ANOVA for multiple groups. For data that doesn’t fulfil those criteria we will use median with interquartile range and Mann-Whitney U-test or Kruskall-Wallis one way analysis of variance, respectively. Intention-to-treat will be used, including all randomized parent-infant dyads in the analysis. The division of group 2 into 2a and 2b, which is a nomenclature to distinguish breastfeeding from no breastfeeding, will be taken into account in the comparative analyses and differences between the two subgroups will be scrutinized. Cohens kappa will be used to calculate interrater reliability between PIPP-R scorers.

The data collected in the study is safely stored on a secure server at Örebro University. The project folder on the server is only available to the researchers in the project and is automatically backed-up. The principal investigator is responsible for the data monitoring, ensuring that the researchers in the study are carrying out the research according to the research protocol, ensuring intervention fidelity in the live parental lullaby singing via recurring spot checks with microanalysis of the live singing, ensuring the research is keeping to time and budget and that the research is being conducted ethically. The research group will meet regularly to ensure consistency. During the original development of the project proposal of the SWEpap-study, the research group consulted with parents with previous extensive experience of NICU care. These parents will continue to give feedback on demand.

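### Excluding non-adherent dyads contradicts intention-to-treat and would break the randomised comparison; losses could be uneven at the hospital that does not use glucose

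*Protocol article*

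**What the plan says.** **Arms.** Under Eligibility criteria, "The infant-parent dyad is randomly assigned to one of three treatment groups; one standard of care group with glucose", the other two being skin-to-skin contact (SSC) and the full combination, with 75 dyads in each. No hospital is exempted. Table 1 describes group 1 thus: "The infant is placed on the examination table for the blood test", with tucking, oral glucose and something to suck.

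**Local practice.** Interventions explains why group 2 is split into 2a and 2b: "standard of care in one of the hospitals does not include glucose but comprises only SSC and breastfeeding when applicable".

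**Handling after randomisation.** Under Recruitment and allocation, after consent "the researcher opens the envelope and the allocated treatment regimen is offered to the parents". The same section ends: "If the parent does not adhere to the protocol in the allocated treatment group, the infant will be excluded from the study".

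**Analysis.** Data analyses, management and monitoring says that intention-to-treat applies and that all randomised dyads enter the analysis. Normally distributed outcomes are "compared with t-test for two groups and ANOVA for multiple groups"; otherwise the choice is "Mann-Whitney U-test or Kruskall-Wallis one way analysis of variance, respectively". None of these tests takes account of hospital.

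**Main contrast.** The Sample size section is built on group 1 versus group 3, with a clinically important difference of 2 PIPP-R points and an SD of about 2.

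**The concern.** The exclusion rule and the intention-to-treat rule give opposite instructions for the same infants. Whether a parent follows the allocated regimen is known only after allocation and can depend on which regimen it is. Dropping those infants therefore leaves groups that are no longer comparable by design. The exclusion may also happen before the venipuncture, so that no PIPP-R score exists and intention-to-treat cannot be restored later.

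The hospital without glucose adds a second layer. Group 1 is called standard care, but at that hospital it is not; SSC, with breastfeeding where applicable, is. Splitting group 2 acknowledges the local standard but does nothing for group 1, the arm furthest from it. If group 1 dyads were lost there more often than group 3 dyads, the two arms would contain different mixes of hospitals. A test on pooled hospitals would then count any difference in PIPP-R level between hospitals as a treatment effect, in either direction. This would fall on the contrast that the trial is sized for.

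**Working it through.** **1. The two rules side by side.** Recruitment and allocation: a non-adherent parent means the infant leaves the study. Data analyses, management and monitoring: all randomised dyads are analysed. If a fraction *p* of an arm is excluded and those infants' mean score differs by *d* from that of the infants kept, the arm mean shifts by *p* × *d*. The article gives neither quantity for any arm, so this part has a mechanism but no computable size.

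**2. The plan's own figure.** The stated 63 per group does not follow from a difference of 2 and an SD of 2, which needs 16 per group (two-sided 0.05, power 0.8). It does match a difference of 1 with SD 2. That is a separate matter; only the 75 per group and SD 2 are used below.

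**3. Hospital bias if group 1 is thinned at one site.** From the article: 75 per group, SD 2, four hospitals. Assumed: equal hospitals, so 75/4 ≈ 19 per arm at the no-glucose site and 56 elsewhere; a PIPP-R level there that differs by D = 1 point from the others; losses only in group 1 at that site; no replacement.

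Bias = (site's share of group 3 − site's share of group 1) × D. With k group 1 infants kept at that site:

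| k kept of 19 | Share in group 3 | Share in group 1 | Bias (points) | Type I error, pooled t-test |
|---|---|---|---|---|
| 19 | 19/75 = 0.253 | 19/75 = 0.253 | 0 | 0.044 |
| 14 | 0.253 | 14/70 = 0.200 | 0.05 | 0.047 |
| 10 | 0.253 | 10/66 = 0.152 | 0.10 | 0.055 |
| 9 | 0.253 | 9/65 = 0.138 | 0.115 | 0.059 |
| 0 | 0.253 | 0 | 0.25 | 0.104 |

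The error rates come from 40,000 simulated trials with no true effect. A model with arm and hospital gave bias 0.00 and type I error 0.048 to 0.051 in every row. On rounded scores (8,000 runs), the pooled Mann-Whitney test gave 0.054 at k = 10 and 0.102 at k = 0; the van Elteren test gave 0.050 in both.

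**4. Other assumptions.**
- D = 0.5 with all lost: bias 0.13, type I error 0.064.
- Losses replaced from other hospitals to keep 75, D = 1: half lost 0.125 points (0.064); all lost 0.25 points (0.118).
- D = 2 at a 25% share, normal approximation: half lost 0.21 points (0.097); all lost 0.50 (0.294).
- 40% share, D = 1, all lost, normal approximation: 0.40 points (0.186).

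**5. Precision of a within-hospital comparison.** With SD 2, the unadjusted SE is 2√(1/n₁ + 1/n₃). The adjusted SE is 2/√w, where w sums n₁n₃/(n₁ + n₃) over the site and the rest.
- All retained: unadjusted 2√(1/75 + 1/75) = 0.327. Adjusted w = 28 + 9.5 = 37.5, so 2/√37.5 = 0.327.
- k = 10: unadjusted 2√(1/66 + 1/75) = 0.338. Adjusted w = 28 + (10 × 19)/29 = 34.55, giving 0.340.
- k = 0: unadjusted 2√(1/56 + 1/75) = 0.353. Adjusted 2√(2/56) = 0.378, because only hospitals with both arms contribute.

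At 2 points and SD 2, power with 56 per group is 0.9995. With 47 per group (63 × 3/4, after the planned losses) it is 0.998.

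**The case against.** The case against the hospital part is strong. The bias needs a chain of events, none of them documented: group 1 is delivered at that hospital, its dyads there drop out more than group 3's, they leave the analysis, and PIPP-R levels differ between hospitals. The exclusion rule turns on the parent, who consented before allocation, whereas the passage on local practice describes staff routine. Group 1 asks least of parents. Group 3 asks most, and the Discussion itself expects some shyness about singing, so non-adherence could just as well thin group 3. All of this stands.

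It is also fair that a hospital term is commonly left to a statistical analysis plan, which is not shown. Its absence from the article is not an error in itself.

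A reader might infer that group 1 is bound to be depleted at the no-glucose hospital, so that group 1 versus group 3 is confounded with hospital. The article does not support that: it gives no adherence rates, site shares or hospital effects, and the route closes if the intention-to-treat rule is followed and scores are kept. A reader might also take the Discussion's remark about the ethics of departing from local guidelines to mean that group 1 is not used there. That remark concerns not preventing breastfeeding and does not settle the matter.

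None of this touches the contradiction between the two rules, which is on the page and needs no conjecture about hospitals.

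**Conclusion.** The firm defect is the contradiction. If the exclusion rule is followed, the comparison is no longer the randomised one, in any arm and at any hospital, by an amount that cannot be computed in advance.

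The hospital part is conditional and small. It is zero if group 1 is delivered and retained everywhere, or if intention-to-treat prevails with scores available. With a 25% site share, SD 2 and a 1-point hospital difference, it is about 0.1 points with half of group 1 lost there (type I error about 0.06) and 0.25 points with all lost (about 0.10), against a target of 2 points. Larger values need a bigger hospital difference or a bigger site. The other hospitals still supply a randomised comparison, so even complete loss of group 1 at one site would confound only partly. The correction is worth making because it is cheap, not because harm is shown.

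**What to change.** 1. Delete the rule that excludes infants of non-adherent parents. Film and score every randomised infant whatever regimen is actually received, and analyse each one with a PIPP-R score in the allocated arm.
2. State whether group 1 is randomised and delivered at the hospital whose standard care has no glucose. If it is not, use that hospital only for group 3 versus group 2.
3. Compare group 1 with group 3 within hospital: arm and hospital as fixed factors, or a van Elteren test if ranks are needed.

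Step 3 does not remove selection within a hospital caused by exclusions; only step 1 does.

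The cost is one model term. The SE stays at 0.327 when all infants are retained and is about 0.34 either way with half of group 1 lost at that site. It rises noticeably, from 0.353 to 0.378, only if that hospital has no group 1, and power at the stated 2 points and SD 2 then remains at least 0.998.
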